#### Economic evaluation

The type of economic evaluation by a health economist will depend on the results. It is possible that there will be a difference in efficacy, so a cost effectiveness or cost-utility analysis will be appropriate. If one intervention were more effective and less expensive, an incremental cost effectiveness (utility) ratio (ICER) would not need to be calculated as it would be clear that the more effective intervention is preferred. If one intervention were more effective and more expensive, then an ICER would need to be calculated. If the results show that one intervention is equally effective to the alternative(s), then a cost-minimisation analysis is appropriate. In this case, there is no difference in effectiveness so the economic analysis would be a comparison of costs only; if one intervention is cheaper, it is the preferred alternative.

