**Methods:**

Participants with symptoms of dizziness described as imbalance, together with a painful and/or stiff neck will be recruited via media releases, advertisements and mail-outs to medical practitioners in the Hunter region of NSW, Australia. Potential participants will be screened by a physiotherapist and a neurologist to rule out other causes of their dizziness. Once diagnosed with cervciogenic dizziness, 90 participants will be randomly allocated to one of three groups: Maitland mobilisations plus range-of-motion exercises, Mulligan SNAGs plus self-SNAG exercises or placebo. Participants will receive two to six treatments over six weeks. The trial will have unblinded treatment but blinded outcome assessments. Assessments will occur at baseline, post-treatment, six weeks, 12 weeks, six months and 12 months post treatment. The primary outcome will be intensity of dizziness. Other outcome measures will be frequency of dizziness, disability, intensity of cervical pain, cervical range of motion, balance, head repositioning, adverse effects and treatment satisfaction. Economic outcomes will also be collected.

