#### Secondary outcomes

1) Frequency of dizziness will be measured on a six-point rating scale (0 = no dizziness, 1 = dizziness less than once per month, 2 = 1–4 episodes of dizziness per month, 3 = 1–4 episodes of dizziness per week, 4 = dizziness once daily, 5 = dizziness more than once a day or constant). This scoring method has been used by several researchers 
[4,8,37,38] to measure frequency of dizziness.

2) Disability caused by dizziness will be measured with the Dizziness Handicap Inventory (DHI). This is a health status measure specifically designed to assess dizziness. The DHI assesses the quality of life using three subscales evaluating the impact of dizziness on the functional, emotional and physical aspects of everyday life 
[40]. The highest possible score is 100, indicating maximum self-perceived handicap. The DHI has been shown to be a highly reliable and responsive tool 
[40-42].

3) Severity of neck pain (an average level over the previous week) will be assessed with a 100 mm VAS. There is much evidence supporting the high validity of the VAS for measuring pain intensity 
[43-47].

4) Global perceived effect will be used to assess satisfaction with treatment and measured by self-assessment on a six-point scale (0 = no benefit, 1 = minimal benefit, 2 = some benefit, 3 = a lot of benefit, 4 = great benefit, 5 = maximal benefit) as used in other studies 
[4,48,49].

5) Posturography will be used to identify and quantify disturbances in balance. Body sway will be measured with a Chattecx Balance Dynamic System (Serial No 1001, Chattecx Corporation, the Chattanooga Group, Tennessee). Recordings will be performed during the following tasks.

· standing erect with the neck in the neutral position with eyes open

· standing erect with the neck in the neutral position with eyes closed

· standing erect with the neck extended

· standing erect with the neck in left rotation

· standing erect with the neck in right rotation

· standing on a moving platform.

Posturography has been used in many studies to assess people with dizziness and has been found to have good correlations with the participant’s symptoms 
[4,6,8,37].

6) A Cervical Range of Motion (CROM) goniometer (Performance Attainment Associates, [name]), which has been shown to be a reliable tool with good validity 

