[50], will be used to measure cervical spine movements. Active flexion, extension, left and right rotation, and left and right lateral flexion will be measured. Each movement will be measured three times and the average taken.

7) Neck repositioning sense will be assessed with the CROM device. This task tests the participant’s ability to accurately reposition their head and neck. The participant is first seated with their head in a neutral position. They are then asked to close their eyes and to move their head into rotation. At mid-range of rotation, the participant will be asked to stop, hold their head steady and think about their position. This position is referred to as the ‘target position’. After 5 seconds, the participant returns to the starting position and then attempts to find the target position again at which point a reading is taken. The number of degrees difference between the target position and the attempt to find it are calculated. This is performed three times for both right and left rotation and the average taken for each direction of rotation movement.

Information about adverse events will be collected by the treating physiotherapist at each treatment session and by the research assistant at each follow-up measurement session using open-ended questions as per normal clinical practice.

Participants will be given a diary and asked to log medication use, visits to a medical practitioner, visits to other health professionals, time off work, changes in social engagements and adherence to home exercises.

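### The economic plan switches to a cost-only comparison when treatments are judged equally effective, but never defines equal, so a non-significant result is likely to be taken as no difference

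*Protocol article*

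**What the plan says.** The Economic evaluation section opens with "The type of economic evaluation by a health economist will depend on the results". If efficacy differs, it expects a cost-effectiveness or cost-utility analysis, with an incremental ratio when the more effective option also costs more. The other branch reads: "If the results show that one intervention is equally effective to the alternative(s), then a cost-minimisation analysis is appropriate". In that case, the section continues, "there is no difference in effectiveness so the economic analysis would be a comparison of costs only; if one intervention is cheaper, it is the" option to choose.

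The effectiveness criteria are in two other sections. Sample size calculation bases the trial on independent t-tests for differences between pairs of groups at alpha 0.05. Statistical methods judges effect by the p-value of a time-by-group interaction in a mixed model, with t-tests at each time point. It also sets a gatekeeping order: SNAG versus placebo, then Maitland versus placebo, and SNAG versus Maitland only if those results are significant at 5%. No section gives an equivalence margin, an equivalence test or a confidence-interval rule. Cost effectiveness is listed among the other aims under Study aims, and the Discussion repeats it for all three pairwise comparisons.

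**The concern.** The branch is a stated decision rule with a consequence, not a detail left for later. Once it applies, the estimated difference in effect is set to zero and cost alone decides. What triggers it is undefined. The only tools that the article supplies are difference tests, and failing to reject such a test does not show equality. In a trial sized for a large effect, a moderate true difference will often be missed.

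At stake is the economic conclusion: a cheaper but less effective treatment could be recommended. Such a treatment may still be a reasonable choice at some value per unit of benefit, but under this branch that trade-off is never examined. The primary efficacy test is not affected.

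**Working it through.** **Inputs (Sample size calculation).** 30 per group; DHI SD 15, target difference 11, power 80%; VAS on a 0–10 scale, SD 2.4, target difference 2; alpha 0.05. Two-sided testing is assumed, because the article does not state it.

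**The plan's own figure.** n per group = 2 × (1.960 + 0.842)² × (15/11)² = 29.2, which rounds up to 30. Power at 30 is 81.1% by the normal approximation and 79.8% by the noncentral t. The DHI calculation reproduces. The VAS inputs give 23 per group (24 by the t distribution), so 30 gives about 89% power for 2 units.

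**Standard errors and interval widths.** SE = SD × √(2/30).
- DHI: 15 × 0.2582 = 3.873. The 95% half-width is 2.002 × 3.873 = 7.75 points.
- VAS: 2.4 × 0.2582 = 0.620. The 95% half-width is 2.002 × 0.620 = 1.24 units.

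An observed DHI difference of 7 would be non-significant, with an interval from 7 − 7.75 = −0.75 to 7 + 7.75 = 14.75. That interval includes the 11-point target.

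**Probability of a non-significant result.** Noncentral t with 58 degrees of freedom and noncentrality = true difference / SE:

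| Outcome | True difference | Noncentrality | P(non-significant) |
|---|---|---|---|
| DHI | 5.5 | 1.42 | 71% |
| DHI | 7 | 1.81 | 57% |
| DHI | 11 (target) | 2.84 | 20% |
| VAS | 1 | 1.61 | 65% |
| VAS | 2 (target) | 3.23 | 11% |

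**Gatekeeping.** I simulated 100,000 three-arm trials on the DHI, with 30 per group, SD 15 and pooled variance.
- If both treatments truly beat placebo by 11 points, SNAG versus Maitland is reached in about 69% of trials.
- If the true benefits are 11 and 5.5 points, it is reached in about 28% and is significant in about 3%. Without the gate it would be significant in about 29%.

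In the second case the head-to-head comparison would seldom yield a formal difference although one exists.

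**What a margin would do.** The article gives no margin, so these margins are assumptions. They use two one-sided tests at 5%, a true difference of zero and the normal approximation.
- DHI: margin 11 gives about 77% power. Margin 5.5 cannot be met, because the 90% half-width is 6.47.
- VAS: margin 2 gives about 89% power. Margin 1 cannot be met, because the 90% half-width is 1.04.

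**From non-significance to a wrong preference.** The worse arm must also be the cheaper one. If that were certain, and every non-significant result were read as equal, the table would give the probability of preferring the worse arm. If the worse arm were certain to cost more, the probability would be zero. The article has no cost data to place the trial between these limits.

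**The case against.** The section never mentions a p-value. It hands the evaluation to a health economist, who might apply a sensible standard of equality. That stands: reading equality as non-significance is an inference about what is likely, not something the text says. The data could also support an equivalence claim. If the planned differences of 11 and 2 were taken as margins, power would be about 77% and 89%. So it is too strong to say that the results could never show equality; the defect is that no rule is stated.

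At the planned differences the miss rates are 20% and 11%; the larger figures belong to smaller true effects. The calculation uses a single-time-point t-test, and the mixed model may be more precise, but the article gives no inputs for that. These points limit the size of the problem. They do not repair a branch that sets an uncertain difference to zero.

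Two stronger readings are tempting:
- A reader might infer that cost-utility analysis is impossible. The section says "so a cost effectiveness or cost-utility analysis will be appropriate", while the DHI is described thus: "This is a health status measure specifically designed to assess dizziness". The diary items read "log medication use, visits to a medical practitioner, visits to other health professionals, time off work, changes in social engagements and adherence to home exercises", and no utility instrument is listed. But the abstract says "Economic outcomes will also be collected" without itemising them, and a condensed article may leave the instrument to the full protocol. The wrong-preference risk does not depend on this point in any case.
- A reader might infer that the rule for a more effective and less expensive option ignores sampling uncertainty. The text is only silent on this, and such methods commonly sit in an analysis plan.

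**Conclusion.** The concern holds for the cost-minimisation switch. The results choose the form of evaluation, the trigger is undefined, and the only effectiveness criteria at hand are difference tests at 5%. On the trial's own inputs, a true difference of half the DHI target would be non-significant about 71% of the time, and half the VAS target about 65%; at the full targets the figures are 20% and 11%. These rest on two-sided 5% pairwise t-tests, complete data on 30 per group, and the stated standard deviations. They are probabilities of missing a difference, not of a wrong recommendation, which also depends on unknown costs.

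The article does not support the claim that no utility measure is collected, or that uncertainty will be ignored when one option is both better and cheaper. Neither is part of this finding. The point deserves correction because cost effectiveness is a stated aim, but it does not touch the efficacy analysis.

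**What to change.** Fix the type of evaluation before results are seen. For all three comparisons, estimate incremental cost and incremental effect jointly, whatever the p-value and whether or not the gatekeeping order reaches the comparison. Name the effect measure in advance (dizziness VAS or DHI). Show uncertainty with bootstrapped cost–effect pairs and acceptability curves.

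Delete the cost-minimisation branch. If it is kept, allow it only when the confidence interval for the difference in effect lies wholly within an equivalence margin set and justified beforehand. At 30 per group a margin of half the planned differences could not be met on the calculation above.

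The cost is a few sentences of text and some routine analysis on effect and resource-use data already planned, with no extra participants. The downside is a less clear-cut economic conclusion, because the joint uncertainty will be visible.

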#### Controlling bias

To minimise bias randomisation, concealed allocation, specific inclusion and exclusion criteria, blinded outcome assessment, patient blinding, blind data analysis, and intention to treat analysis have been used. It was not possible to blind the physiotherapist performing the interventions.

## Discussion

This paper outlines the rationale and design for a RCT that compares the effectiveness and cost effectiveness of:

a) SNAGs to a placebo intervention

b) Maitland passive joint mobilisations to a placebo intervention

c) SNAGs to Maitland passive joint mobilisations

in reducing symptoms of cervicogenic dizziness and associated pain over 12 months. The value of this study will be to determine which of two common manual therapy treatments is most effective for this problem and whether manual therapy is effective in the longer term (up to one year). The study will contribute to evidence-based manual therapy leading to improved clinical decision making in this field of clinical practice.
